### Concealment mechanism {16b}

Due to the nature of the trial, participants and therapists in the study cannot be blinded for condition. Assessors and therapists will emphasize the importance of blinding to the participants and remind them not to reveal the randomized treatment condition to the assessors. Therapists are supported by the principal investigator, who is not involved in the execution of the assessments. Assessors will be asked to report any case of unblinding, in which case, another assessor will repeat the entire measurement. The use of a validated password file which is not accessible for those involved in the assessment will ensure concealment until the randomization result is revealed.

### Implementation {16c}

An independent researcher from GGZ Rivierduinen will perform the randomization.

After randomization, the independent researcher will only notify the trial coordinator from the research team, who will inform the therapist and participant.

## Assignment of interventions: blinding

### Who will be blinded {17a}

Both assessors and data analysts will be blinded after assignment to interventions.

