### Trial design {8}

This study is designed as a randomized, controlled, single-blinded two-center superiority trial with two parallel groups. All patients meeting the inclusion criteria are asked for written informed consent to participate in the intervention study. For consenting participants, baseline measures (T0) are completed subsequently. Randomization will be performed as block randomization with a 1:1 allocation stratified per treatment location. An independent researcher will conduct randomized allocation by using the SPSS function to produce random numbers. Hence, the main researcher will be blind to the randomization process. Randomization will take place in blocks of 10 participants. After completing the baseline assessments (T0), participants will be informed in which group they have been randomized. Assessments (see Fig. 1) are scheduled pre-treatment (T0), post-treatment (T1), and at 3-month (T2) and at 6-month (T3) follow-up. Assessment will be done by a team of independent assessors (i.e. trained clinicians and supervised master level students) who are blind for condition. Participants in the waiting list condition are offered EMDR treatment after T1 and are subsequently assessed post-treatment and at 3 and 6 months follow-up (see Fig. 1). For participants in the waiting list condition, T1 will be labelled as T0WL when they enter treatment (*t*_*1*_ = *t*_*0-wl*_).

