## Procedure for unblinding if needed {17b}

The design is open label with only outcome assessors and data analysts being blinded so unblinding will not occur.

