#### Primary study parameter(s)

To investigate the effect of EMDR and waiting on the primary outcome (level of depressive symptoms, CDI-2) and secondary outcome variables (i.e. post-traumatic stress symptoms (CATS), anxiety symptoms (SCARED) and overall social-emotional problems (SDQ)), a linear mixed model analysis will be conducted. A chi-square test will be used to investigate whether there is a difference between conditions in the percentage of MDD diagnoses (K-SADS-PL; MDD, partial remission, full remission) at T1, comparing changes in the waiting list condition (T0–T1; *n* = 32) with changes in the EMDR condition (T0 (*n* = 32) + T0WL(*n* = 32) − T1).

Effect sizes will be calculated using Cohen’s *d.* Based on the mean difference between scores from baseline (T0) to post-treatment (T1) and from baseline (T0) to follow-up (T2, T3), the results will be divided by the pooled standard deviation (Cohen, 1988).

To investigate the predictive effect of baseline post-traumatic stress symptom severity (CATS), emotional abuse and emotional neglect (CTQ), and general family functioning (FAD) on treatment outcome, we will perform a linear mixed model analysis. All predictors will be entered separately and we will conduct Bonferroni post hoc corrections to correct for the number of analyses. The level of significance will be set at *α* = 0.05/4.

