#### Other study parameters

For the prediction analyses, all treated participants, including participants from the former waiting list control group, will be combined. The four predictor variables (baseline post-traumatic stress symptom severity (CATS), emotional abuse, emotional neglect (CTQ) and general family functioning (FAD) scores will be entered separately in the linear mixed model analyses. Bonferroni post hoc corrections will be conducted in order to correct for the number of analyses. The level of significance will be set at *α* = 0.05/4.

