### Composition of the data monitoring committee, its role and reporting structure {21a}

Collection, storage and processing of the data will be performed by the research team, with the assistance of a research assistant and master degree students. Because of the low risks involved in this study, no official data monitoring committee will be formed. To promote data quality, regular data monitoring will be done by an independent peer auditor, not involved in the study. This auditor will randomly check the research file on inclusion pace, drop-outs and general presence of completeness of the data.

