## Data Availability

The researchers of the research team have access to the dataset. Any data required to support the protocol can be supplied on request by other people from the research team and regulatory authorities that are mentioned in the information letter.

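### Analyst blinding is claimed without limit, but it cannot hold for the full longitudinal file or the pooled MDD-status test, and it is not secured for the T0–T1 comparison where it is feasible

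*Protocol article*

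**What the plan says.** Who will be blinded {17a} reads: "Both assessors and data analysts will be blinded after assignment to interventions". Procedure for unblinding if needed {17b} adds: "The design is open label with only outcome assessors and data analysts being blinded so unblinding will not occur". Neither section names a time window, a dataset or a subset of analyses.

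Trial design {8} treats the arms differently after T1: "Participants in the waiting list condition are offered EMDR treatment after T1 and are subsequently assessed post-treatment and at 3 and 6 months follow-up". It also says: "For participants in the waiting list condition, T1 will be labelled as T0WL when they enter treatment".

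The analysis sections use this structure. Under Primary study parameter(s), the chi-square on MDD status compares the waiting list (T0 to T1, 32 participants) with "changes in the EMDR condition (T0 (*n* = 32) + T0WL(*n* = 32) − T1". Secondary study parameter(s) describes the same test as a plain between-condition comparison at T1, with no pooling. Other study parameters says: "For the prediction analyses, all treated participants, including participants from the former waiting list control group, will be combined".

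On who handles the data, the data monitoring section {21a} says: "Collection, storage and processing of the data will be performed by the research team". Data Availability says: "The researchers of the research team have access to the dataset".

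**The concern.** Analyst blinding protects the choices still open when the randomised comparison is run. This plan leaves some open. The MDD-status test is described in two ways. It is set out with three outcome categories in one place, while Hypothesis 1 concerns the percentage meeting MDD criteria. A completer analysis sits beside the intention-to-treat analysis.

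If the analyst can see which participants waited, these choices are made with the arms in view, although the protocol states the opposite. A reader would then credit the trial with a safeguard that parts of its own analysis plan rule out.

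**Working it through.** No sample-size or power figure is involved. The check is whether each planned dataset or analysis could be given to an analyst under neutral arm codes without its structure revealing the arms.

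**Inputs.** The total sample is 64, split equally (Sample size {14}). Per arm this is 64 / 2 = 32, which matches the figures under Primary study parameter(s). The assessment schedule is taken from the text of Trial design {8}, since the timeline figure is not shown.

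**1. Full longitudinal file.**
- EMDR arm: T0, T1, T2, T3, which is 4 occasions.
- Waiting-list arm: T0, T1 (= T0WL), post-treatment, 3 months, 6 months, which is 5 occasions.

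The T0WL label and the fifth occasion exist in one arm only. Coding the arms A and B hides nothing.

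**2. Pooled chi-square on MDD status (Primary study parameter(s)).**
- EMDR side: 32 + 32 = 64.
- Waiting-list side: 32.
- Ratio: 64 / 32 = 2.
- If 30% drop out (the protocol's maximum, assumed equal on both sides): 64 × 0.7 = 44.8 against 32 × 0.7 = 22.4, still 2 to 1.

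The larger side must be EMDR. The same waiting-list participants also supply records to both sides, which identifies them individually. MDD status is one of the two primary outcomes, so this is not confined to exploratory work.

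**3. Randomised T0–T1 comparison.**
- Occasions: 2 in each arm.
- Sizes: 32 against 32.

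The T0–T1 mixed-model comparison for CDI-2, CATS, SCARED and SDQ, and the unpooled T1 chi-square of Secondary study parameter(s), can be run on this file. Without the T0WL label, nothing in its structure shows which code is EMDR.

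**4. Is the analyst kept apart from those who know allocation?**
- Implementation {16c}: the trial coordinator, a member of the research team, is told each allocation.
- Section {5d}: the principal investigator handles contact with the independent researcher who randomises and with the practitioners. The second investigator and the research assistant coordinate assessments so as to stay blind.
- Data management {19}: the principal investigator supervises the case record forms and grants data access.
- Section {21a}: the research team processes the data.

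The team is therefore divided. Some members know allocation and some are kept from it. The article does not place the analyst on either side, and describes no step that withholds the post-T1 data from the analyst.

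**The case against.** The strongest reply is that the conflict is narrow. Analyst blinding matters most for the randomised T0–T1 comparison, and that comparison can be masked under the stated design. This stands. A reader might infer that the stated blinding does not exist at all; the documents do not support that.

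A reader might also infer that the team handling the data knows the allocation. That is not what the article says. Only the trial coordinator is notified, the second investigator and the research assistant are kept blind, and no section names the analyst. The data-processing and data-availability statements do not assign the analysis to anyone. What remains is that the separation is not stated.

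The prediction analyses are weaker evidence than they first appear. They pool all treated participants and contain no between-arm contrast. A data manager could supply pre- and post-treatment records without an arm label, so these analyses do not in themselves force the analyst to know who waited.

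Nor can the harm be expressed as an inflated type I error. An analyst with A/B codes who picks the smaller of two two-sided p-values gains exactly as much as one who sees the arms. That inflation comes from analytic flexibility, and masking does not remove it.

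Finally, export and code-break procedures commonly belong in an analysis plan or full protocol that is not shown, and their absence here is no fault. The point rests on an unqualified positive statement that other sections of the same article contradict. If the pooled chi-square were reconciled to the plain T1 comparison, the main conflict in the primary analyses would go, but the one in the full file would remain.

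**Conclusion.** The statement is wrong as written, in a limited sense. Blinding of data analysts, with unblinding ruled out, cannot hold for the full longitudinal file (5 occasions against 4, with a label unique to one arm) or for the pooled MDD-status test (64 against 32). It can hold for the T0–T1 between-arm comparison (2 occasions, 32 against 32), but the article does not secure it there.

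The size of any bias cannot be derived from the document. The practical effect is probably moderate: the main tests are named in advance, and CDI-2 is completed by adolescents and parents, with participants not blinded in any case.

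The conclusion assumes that the analyst receives either the full file or the pooled dataset as described. Masking also works only by structure: a large difference at T1 could still suggest which code is EMDR. The same sentence of the protocol covers assessor blinding, which is not in question here.

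**What to change.** 1. Have the data manager issue a T0–T1 file with arms coded A and B, no T0WL label, no later visits, and no session or adverse-event records (per-session recording during EMDR would identify the arm). Someone without access to the allocation runs the between-arm analyses for Hypotheses 1 and 2 on this file, and the output is locked and dated.
2. Only then release the post-T1 data for the pooled, follow-up and predictor analyses. A completer analysis that needs session data belongs to this stage.
3. Reword Who will be blinded {17a} and Procedure for unblinding if needed {17b} so that analyst blinding is claimed for the T0–T1 comparison only, and state when the code is broken.
4. Reconcile the MDD-status chi-square under Primary study parameter(s) with the description under Secondary study parameter(s), so that the randomised test is the plain T1 comparison between arms. Any pooled comparison should be labelled as a separate, unblinded analysis.

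The cost is one extra export, a dated lock and a few sentences of text. No added participants, visits or staff are needed, provided that someone already on hand can work without allocation access.

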## Procedure for unblinding if needed {17b}

The design is open label with only outcome assessors and data analysts being blinded so unblinding will not occur.

## Data collection and management

### Plans for assessment and collection of outcomes {18a}

For the primary outcomes (depressive symptoms), different types of measurement—interview and questionnaires—are combined. Secondary outcomes are assessed by questionnaires. Both child and parent versions of the questionnaires will be used. A description of the study instruments can be found in the “Outcomes {12}” section.

The K-SADS interview will be administered via a secured video ZOOM-meeting, using the K-SADS computer tool with pre-programmed diagnostic algorithms based on DSM-5 criteria. The K-SADS interview will include demographic questions. Assessors will receive training in both the application and scoring of the K-SADS interview. All interview reports with allocated classifications are discussed with a supervisor.

All questionnaires will be administered via Qualtrics, an online survey system. Links to the questionnaires will be sent by email, including a unique participant number for every client. Participants and parents receive individual links. At T0, assessment is guided by an assessor via ZOOM video connection to enable participants to ask questions if they encounter difficulties or get support if they experience discomfort.

### Plans to promote participant retention and complete follow-up {18b}

The post-intervention (T1) is part of regular treatment evaluation and is planned in close cooperation with the EMDR therapist. Results of this measurement are handed over to the EMDR therapist, who will take the results into account to evaluate EDMR treatment with the participant, one of the parents and the overall responsible practitioner.

Appointments for follow-up assessments (K-SADS interview) will be made by telephone. One day in advance of the interview appointment, the link to the questionnaires is sent. Prior to the start of the K-SADS interview, the participant is either being thanked for filling in the questionnaires or kindly reminded to do so after the interview. If the participant does not respond within a week, a reminder is sent by email, and if necessary, followed by a phone call.

After the last measurement, participants receive 25 euros as compensation in the form of a gift voucher. To detect drop-out of specific groups, participants who discontinue the treatment programme will be asked to continue measurements.

### Data management {19}

Upon enrolment, each participant will be assigned a unique study ID. This is a substitute of their identity information and the only form of participant referral that will be presented on case report forms and that will be included in statistical analysis.

Under the supervision of the principal investigator, assessors fill in the case record forms and upload data to a secure server. Data are kept in a secured storage and only authorized staff are granted access by the principal investigator. Data completeness will be checked regularly by both our data managers and the independent researcher from GGZ Rivierduinen will regularly check the data files.

Participants can withdraw from the study at any moment without consequences. Data gathered from participants up until their withdrawal will still be used for analyses.

### Confidentiality {27}

The data of participants will be kept strictly confidential. Research data will be stored and managed by the research team. Names will be coded in unique study ID’s so that privacy will be guaranteed. Only researchers committed to this study have access to the coded data.

Non-coded data will be saved separately in locked filing cabinets. Only the research team, the accredited Medical Ethical Committee, and Inspectie Gezondheidszorg en Jeugd (IGJ) will have access to this data file. The confidentiality agreements will be stored in a secured folder on the network of GGZ Rivierduinen.

Data will be stored for a minimum of 15 years, according to guidelines from the Medical Ethical Committee.

### Plans for collection, laboratory evaluation and storage of biological specimens for genetic or molecular analysis in this trial/future use {33}

Not applicable, no samples collected.

## Statistical methods

### Statistical methods for primary and secondary outcomes {20a}

Data will first be summarized by frequency tables and descriptive statistics (mean, standard deviation, number and percentages of cases). To investigate potential group differences regarding demographic and clinical variables between the two conditions, *t*-tests and chi-square tests will be conducted. Summary tables will be provided for all variables at all assessment points. Intention-to-treat analyses will be conducted for all outcomes. Additionally, a completer analysis will be conducted.

#### Primary study parameter(s)

To investigate the effect of EMDR and waiting on the primary outcome (level of depressive symptoms, CDI-2) and secondary outcome variables (i.e. post-traumatic stress symptoms (CATS), anxiety symptoms (SCARED) and overall social-emotional problems (SDQ)), a linear mixed model analysis will be conducted. A chi-square test will be used to investigate whether there is a difference between conditions in the percentage of MDD diagnoses (K-SADS-PL; MDD, partial remission, full remission) at T1, comparing changes in the waiting list condition (T0–T1; *n* = 32) with changes in the EMDR condition (T0 (*n* = 32) + T0WL(*n* = 32) − T1).

Effect sizes will be calculated using Cohen’s *d.* Based on the mean difference between scores from baseline (T0) to post-treatment (T1) and from baseline (T0) to follow-up (T2, T3), the results will be divided by the pooled standard deviation (Cohen, 1988).

To investigate the predictive effect of baseline post-traumatic stress symptom severity (CATS), emotional abuse and emotional neglect (CTQ), and general family functioning (FAD) on treatment outcome, we will perform a linear mixed model analysis. All predictors will be entered separately and we will conduct Bonferroni post hoc corrections to correct for the number of analyses. The level of significance will be set at *α* = 0.05/4.

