#### Secondary study parameter(s)

To investigate the effect of EMDR and waiting on secondary outcome variables (i.e. post-traumatic stress symptoms (CATS), anxiety symptoms (SCARED) and overall social-emotional problems (SDQ)), a mixed model analysis will be conducted. A chi-square test will be used to investigate whether there is a difference between the conditions in the percentage of MDD diagnosis (K-SADS-PL) at T1.

Effect sizes will be calculated using Cohen’s *d*. Based on the mean difference between scores from baseline (T0) to post-treatment (T1) and from baseline (T0) to follow-up (T2, T3), the results will be divided by the pooled standard deviation.

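### The chi-square test for MDD diagnosis puts the same 32 waiting-list participants on both sides, so it is not the randomised comparison, and it conflicts with the plan's second statement of that test

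*Protocol article*

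**What the plan says.** The Abstract and Hypothesis 1 name the percentage of patients meeting MDD criteria as a primary outcome, beside the CDI-2 score. Four statements bear on its test.

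- **Primary study parameter(s).** "A chi-square test will be used to investigate whether there is a difference between conditions in the percentage of MDD diagnoses" at T1, with K-SADS categories MDD, partial remission and full remission. The control side is given as "comparing changes in the waiting list condition (T0–T1; *n* = 32"). It is compared "with changes in the EMDR condition (T0 (*n* = 32) + T0WL(*n* = 32) − T1").
- **Trial design {8}.** Allocation is 1:1 to two parallel groups. The waiting-list group is treated after its T1: "Participants in the waiting list condition are offered EMDR treatment after T1 and are subsequently assessed post-treatment". The label is then explained: "For participants in the waiting list condition, T1 will be labelled as T0WL when they enter treatment".
- **Secondary study parameter(s).** The same chi-square appears again, now simply as a test of a "difference between the conditions in the percentage of MDD diagnosis (K-SADS-PL) at T1", with no T0WL records added.
- **Statistical methods {20a}.** "Intention-to-treat analyses will be conducted for all outcomes".

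Other study parameters separately announces that all treated participants, former waiting-list members included, are combined for the prediction analyses.

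**The concern.** Pooling treated participants is reasonable when predictors of response are studied. It is not reasonable in the test of EMDR against waiting. Three things go wrong.

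1. Each waiting-list participant contributes one outcome to the control side and another to the EMDR side. A Pearson chi-square assumes that all observations are independent.
2. Half of the EMDR side was randomised to waiting list. The contrast is no longer between the arms as randomised, which is what the parallel-group design and the intention-to-treat statement promise.
3. Time is mixed with treatment. Crossed-over participants are assessed after six weeks of waiting and six weeks of treatment, controls after six weeks only. Anyone who recovers with time has longer to do so on one side.

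The same test is also defined in two ways, so the choice between them could be made after the data are seen. At stake is whether the p-value for a primary outcome measures the randomised effect at all.

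**Working it through.** **Counts.** Sample size {14} gives 64 participants, equally divided, so 64/2 = 32 per arm. The test as printed has 32 on the control side and 32 + 32 = 64 on the EMDR side, that is 96 outcomes from 64 people, with 32 people counted twice. The protocol gives no power or error figure for this test to reproduce; its sample size rests on the CDI-2.

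**Assumptions.** EMDR has no effect. Each adolescent still depressed has chance p of lasting remission in any six weeks. All 32 waiting-list participants cross over and none relapses. The three diagnosis categories are collapsed to remitted or not. The documents give no waiting-list remission rate, so p runs from 10 to 40%. Error rates come from enumerating the binomial outcomes exactly, with two-sided alpha 0.05 (2.5% per direction).

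**Expected remission on the EMDR side.** The control rate is p.
- (A) Final diagnosis status counted: [p + 1 − (1 − p)²]/2. At p = 0.2 this is (0.20 + 0.36)/2 = 0.28.
- (B) Only new remission after T0WL counted, denominator 64: [p + p(1 − p)]/2. At p = 0.2 this is (0.20 + 0.16)/2 = 0.18.
- (C) New remission counted only among those still depressed at T0WL: p.

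| p | A: EMDR side v control | A: false positives for EMDR | B: EMDR side v control | B: false rejections against EMDR | C: total error |
|---|---|---|---|---|---|
| 10% | 14.5 v 10% | 2.4% | 9.5 v 10% | 3.9% | 5.0% |
| 20% | 28.0 v 20% | 5.6% | 18.0 v 20% | 6.2% | 5.2% |
| 30% | 40.5 v 30% | 10.0% | 25.5 v 30% | 9.4% | 5.0% |
| 40% | 52.0 v 40% | 13.5% | 32.0 v 40% | 15.0% | 5.0% |

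Under A the spurious gain is 4.5, 8.0, 10.5 and 12.0 points. The 32 v 32 comparison at T1 has total error of 5.1 to 5.6% over the same range.

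**Standard error, reading A, p = 20%.** With a common rate of 20%, the chi-square standard error is √[0.2 × 0.8 × (1/64 + 1/32)] = √0.0075 = 0.087. With the rate pooled over both sides, (64 × 0.28 + 32 × 0.20)/96 = 0.253, it is √[0.253 × 0.747 × 0.046875] = 0.094.

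For the true value, write the difference as (E + W₂ − 2W₁)/64. Here E is the number remitted in the EMDR arm, W₁ the number of waiting-list participants remitted at T1, and W₂ the number remitted after their treatment. Per waiting-list person, W₂ − 2W₁ is −1 with chance 0.20, +1 with chance 0.16, and 0 otherwise. Its variance is 0.36 − 0.04² = 0.3584. Per EMDR person the variance is 0.16. The standard deviation is √[32 × (0.3584 + 0.16)/64²] = 0.064. The test's standard error is therefore too large.

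With equal remission rates on both sides and a within-person correlation of 0.3 to 0.6, two-sided error falls to about 2.9 to 1.2%. Overlap alone is conservative; the false positives under A come from the extra uncontrolled six weeks.

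**The case against.** It can be said in the plan's favour that the Secondary study parameter(s) section already states the right test, that the Primary section speaks of changes and starts the crossover records at T0WL, and that EMDR therefore gets no credit for recovery while waiting. The first point shows that the repair is near at hand, but it leaves two definitions of one primary test. The second is a fair reading, and it limits what can be claimed.

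A reader might infer that the pooled test favours EMDR and inflates false positives. The documents do not support that as a general statement. It holds under reading A, and not at p = 10% even there. Under B the bias runs against EMDR, and under C the error is about nominal. C, however, is not written anywhere: no section limits crossover or counting to those still depressed at T0WL, and that rule would leave out randomised participants.

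A reader might also infer that anyone without a T1 interview is dropped, against intention-to-treat. The article does not say so. It plans continued measurement after treatment drop-out, and the handling of missing diagnoses is commonly left to an analysis plan.

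What stands untouched is the double use of the 32 people. The counts are printed, so this is a stated method and not a gap.

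**Conclusion.** The concern holds: as written in the Primary study parameter(s) section, the test of the MDD-diagnosis outcome is not the randomised comparison, violates the independence its method requires, and disagrees with the Secondary study parameter(s) section. This follows from the text alone. It should be corrected before analysis.

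The size and sign of the resulting error do rest on assumptions, namely the remission rate p, no relapse, full crossover, and above all the unstated counting rule. Across p of 10 to 40%, error in the affected direction ranges from roughly nominal to about 13.5% for EMDR (reading A) or 15.0% against it (reading B). That one sentence can yield opposite biases is itself a reason to rewrite it.

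The point concerns one of the two primary measures. The CDI-2 has its own linear mixed model and is not affected.

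**What to change.** Define the test once: the arms as randomised at T1 only, 32 EMDR v 32 waiting list, on whether MDD criteria are met, with a risk difference and 95% confidence interval. The Secondary study parameter(s) wording already implies this comparison, and no covariate model is needed. Report the pooled treated cohort (T0 and T0WL to post-treatment) only as a within-person descriptive result, without a between-condition p-value. Make the Primary and Secondary sections say the same.

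This changes wording only and needs no new data. The cost is that the EMDR side falls from 64 records to 32. The table gives exact power of the unadjusted chi-square for 60.9% remission on EMDR, the pilot figure in Background and rationale {6a}. That figure comes from treatment completers, so it may be optimistic for an intention-to-treat analysis. Waiting-list remission is assumed.

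| Waiting-list remission | 32 per arm | 22 per arm |
|---|---|---|
| 20% | 94% | 81% |
| 30% | 74% | 55% |
| 40% | 42% | 28% |

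The last column applies the full 30% drop-out from Sample size {14} already at T1 (64 × 0.70 = 44.8, about 22 per arm). That is a worst case, because the 30% also covers follow-up. Power is good if few adolescents remit while waiting and weak if many do. Counting the waiting-list group twice does not remedy that.

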### Objectives {7}

Building on the study by [name] et al. [35], the current study aims to investigate whether EMDR therapy is more effective in comparison to a waiting list control condition.

#### Hypothesis 1

EMDR therapy is associated with a significant decrease in severity of depressive symptoms and decrease in percentage of patients meeting DSM-5 criteria for MDD compared to the waiting list.

Outcome measures: Total score on the CDI-2 and the percentage of patients meeting DSM-5 criteria for MDD (K-SADS-PL-5).

#### Hypothesis 2

After treatment with EMDR, participants report less comorbid PTSD, anxiety and social/emotional symptomatology in comparison to those in the waiting list control condition.

Outcome measures: severity of PTSD (CATS), anxiety (SCARED) and social/emotional symptoms (SDQ).

The second aim of this study is to investigate predictors of treatment outcome. We will test the following predictors: baseline PTSD symptoms (CATS), family functioning (FAD) and experienced emotional abuse or emotional neglect in childhood (CTQ).

#### Hypothesis 3

A higher level of post-traumatic stress symptoms at baseline predicts a stronger post-treatment reduction in depressive symptoms.

Outcome measures: reduction of depressive symptoms (CDI-2 total score), severity of post-traumatic stress symptoms (CATS total score).

#### Hypothesis 4

A higher level of family dysfunction at baseline predicts smaller post-treatment reductions of depressive symptomatology.

Outcome measures: severity of depressive symptoms (CDI-2 total score), family functioning (FAD, general functioning score and dimension scores).

#### Hypothesis 5

A higher level of emotional abuse or neglect at baseline predicts smaller post-treatment reductions of depressive symptomatology.

Outcome measures: reduction of depressive symptoms (CDI-2 total score), experience of emotional abuse or neglect (respective subscales CTQ).

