## Interventions

### Explanation for the choice of comparators {6b}

Effectiveness of EMDR is compared to an inactive condition (waiting list). To our knowledge, this is the first study investigating the effectiveness of EMDR therapy on the reduction of adolescent depressive symptoms. The waiting list control group serves two purposes. First, it provides an untreated comparison for the EMDR group to determine if EMDR therapy is effective in this specific group. Second, it allows the wait-listed participants the opportunity to obtain the EMDR intervention after 6 weeks.

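### The only planned effect size, Cohen's d, is worded as a change from baseline with no between-arm term, so it does not measure the EMDR versus waiting-list contrast that the trial is designed to estimate

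*Protocol article*

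**What the plan says.** Under Statistical methods {20a}, Primary study parameter(s), the numerator of Cohen's d is given as: "Based on the mean difference between scores from baseline (T0) to post-treatment (T1) and from baseline (T0) to follow-up (T2, T3"). The Secondary study parameter(s) section repeats the rule, starting "Based on the mean difference between scores from baseline (T0) to post-treatment (T1") and ending "the results will be divided by the pooled standard deviation". Neither section says whether the SD is pooled over arms or over time points, and neither names an arm. No other effect size is defined in the article.

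The question the trial asks is a comparison. Objectives {7} states that "the current study aims to investigate whether EMDR therapy is more effective in comparison to a waiting list control condition", and Hypotheses 1 and 2 are both framed against the waiting list. The section on the choice of comparators {6b} says of the control arm that "it provides an untreated comparison for the EMDR group to determine if EMDR therapy is effective in this specific group". Trial design {8} adds: "Participants in the waiting list condition are offered EMDR treatment after T1".

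The tests are specified separately: a linear mixed model for CDI-2, CATS, SCARED and SDQ, and a chi-square test for MDD status at T1.

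**The concern.** An effect size should be on the same contrast as the hypothesis it accompanies. Here the hypotheses compare EMDR with waiting, but the stated formula takes a change over time and does not subtract the change under waiting.

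That matters in this population. Participants enter while meeting criteria for MDD, so some improvement without treatment, and some regression to the mean, are plausible over six weeks. A change from baseline contains both, together with any effect of EMDR, and cannot separate them. The waiting list is in the design to make that separation, and the d as worded does not use it. Because this is the only effect size defined for the continuous primary outcome, readers and later meta-analysts may take it as the treatment effect.

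**Working it through.** **Step 1. Which reading fits the wording?** One rule is given for three time points.

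| Interval | Untreated arm available? | Can the rule be a contrast with untreated control? |
|---|---|---|
| T0 to T1 | Yes | Only if a between-arm term is added that the text does not state |
| T0 to T2 | No, waiting list offered EMDR after T1 | No |
| T0 to T3 | No, same reason | No |

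The reading that fits all three rows is pre-post change.

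**Step 2. How the two measures differ.** Let C_E and C_W be the mean T0-to-T1 improvements in the EMDR and waiting-list arms, with a common SD.

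- Pre-post d in the EMDR arm = C_E / SD
- Randomised d = (C_E − C_W) / SD
- Hence pre-post d = randomised d + C_W / SD

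The excess is exactly the waiting-list improvement in SD units. If the waiting list does not change, the two measures coincide.

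**Step 3. Inputs.** The article gives no waiting-list change and no SD, so there is no figure of its own to reproduce here. Two assumptions are needed.

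- C_W / SD = 0.2, 0.3 or 0.5. This is assumed; no source is given in the article.
- Randomised d = 0.80. This follows from the planning value f = 0.40 in Sample size {14} as d = 2f = 2 × 0.40, if that f is a between-group f, which the section does not state. Values of 0.30 and 0 are added to show the range.

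**Step 4. Results.**

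| Assumed waiting-list change (SD) | True d = 0.80 | True d = 0.30 | True d = 0 |
|---|---|---|---|
| 0 | 0.80 | 0.30 | 0 |
| 0.2 | 1.0 | 0.5 | 0.2 |
| 0.3 | 1.1 | 0.6 | 0.3 |
| 0.5 | 1.3 | 0.8 | 0.5 |

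For a true 0.80 the relative excess is 0.2/0.80 = 25% to 0.5/0.80 = 62.5%.

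**Step 5. Check by simulation** (32 per arm, equal SDs, pre-post correlation 0.5, 4,000 replicates). With a true d of 0.80, the average pre-post d was 1.01, 1.11 and 1.32 for waiting-list changes of 0.2, 0.3 and 0.5 SD; the between-arm difference in change over the pooled baseline SD averaged 0.81 to 0.82. With a true d of 0, the pre-post d averaged 0.20, 0.30 and 0.51, and the between-arm version stayed within 0.01 of zero. This agrees with the formula.

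**The case against.** The best defence is that the sentence is condensed. It follows a paragraph on the effects of EMDR and of waiting and on a difference between conditions, and it names no arm. A pooled SD could be pooled over arms, so the T0-to-T1 value could have been meant as a difference in change between arms. That leaves some room at T1 and none at T2 or T3 for a contrast with untreated control. If it was the intention, the text does not say so, and the same rewording is needed.

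Other parts of the defence stand:

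- The mixed model and the chi-square test do not depend on this d. A reader might infer that the test of Hypothesis 1 or 2 is compromised by it; the article does not support that.
- The article promises summary tables for all variables at all assessment points. If these are given by condition, a reader could derive the between-arm figure. If d is reported for each arm, the waiting-list value would show the drift.
- Changes to T2 and T3 are not errors in themselves. Once the waiting list is treated, uncontrolled change is all the design can offer there.

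It is also tempting to say that the trial's headline result will look several times larger than the d = 0.29 cited in the Background for psychological treatment. The article does not call this d a headline, does not say that 0.29 is a between-group figure, and plans no such comparison. On the assumptions above, most of the gap would in any case be assumed true effect: 0.80/0.29 is already about 2.8, against 1.0/0.29 = 3.4 and 1.3/0.29 = 4.5.

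**Conclusion.** The point holds as a defect in effect-size reporting that should be corrected. The article fixes a formula, twice, that omits the randomised contrast and defines no other effect size. This is more than detail left to an analysis plan: followed as written, the rule yields an uncontrolled change.

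The direction is clear if the waiting list improves: the pre-post d is then too large by that improvement in SD units. The size is not known. The range of 1.0 to 1.3 for a true 0.80, and 0.2 to 0.5 for a true 0, rests on an assumed waiting-list change of 0.2 to 0.5 SD and on equal SDs; the 0.80 also requires f = 0.40 to be a between-group f. These figures illustrate the mechanism and should not be cited as a predicted bias.

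**What to change.** In both Primary study parameter(s) and Secondary study parameter(s), define the main Cohen's d for each continuous outcome as the model-estimated EMDR minus waiting-list difference at T1, given T0, divided by the pooled baseline SD of the two randomised arms, and report it with a 95% CI. Keep the within-arm standardised changes from T0 to T1, T2 and T3 as descriptive figures, shown by arm and labelled as uncontrolled.

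The cost is a few sentences of wording. No new data, visits or participants are needed. The downside for the sponsor is that the reported d will probably be smaller.
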